## Abstract

**Objectives:**

It is uncertain what the effects of introducing digital breast tomosynthesis (DBT) in the Dutch breast cancer screening programme would be on detection, recall, and interval cancers (ICs), while reading times are expected to increase. Therefore, an investigation into the efficiency and cost-effectiveness of DBT screening while optimising reading is required.

**Materials and methods:**

The Screening Tomosynthesis trial with advanced REAding Methods (STREAM) aims to include 17,275 women (age 50–72 years) eligible for breast cancer screening in the Netherlands for two biennial DBT screening rounds to determine the short-, medium-, and long-term effects and acceptability of DBT screening and identify an optimised strategy for reading DBT. The control group will consist of 86,400 women selected from the database of the Dutch breast cancer screening programme screened with digital mammography. The intervention group will undergo DBT examinations only. Four different reading strategies will be evaluated on a subset of first-round screening exams. These four strategies will also be evaluated combined with replacing one of the two readers with AI predictions. The Microsimulation Screening Analysis (MISCAN)-Breast model will be used to estimate the long-term outcomes of DBT screening assuming the best-performing reading method.

**Results:**

The primary outcome measure is the IC and advanced cancer rate at the second round (combined endpoint) in the DBT group compared to the control group. Secondary outcome measures are participation, recall and detection rates, positive predictive value, acceptability, reading method with the best case-based area under the curve and reading time, predicted breast cancer mortality, number of cancers overdiagnosed, and cost-effectiveness.

**Key Points:**

***Question***
* The short-, medium-, and long-term effects of digital breast tomosynthesis (DBT) imaging in the Dutch breast cancer screening programme are unknown, but essential to decide about implementation.*

***Findings***
* This protocol paper describes the primary endpoint of the STREAM trial: the combined interval and advanced cancer detection rate at the second DBT round.*

***Clinical relevance***
* The STREAM trial is a prospective, non-randomised, population-based study in the Dutch breast cancer screening programme, that aims to evaluate the effects and acceptability of two rounds of DBT screening to determine if DBT can enhance the programme’s outcomes.*

**Graphical Abstract:**

[figure not shown]

## Introduction

The Dutch breast cancer screening programme, hereafter the programme, offers a biennial digital mammography (DM) examination to asymptomatic women aged 50 to 75. Craniocaudal (CC) and mediolateral-oblique (MLO) examinations are double-read by two screening radiologists independently and women with suspicious findings are referred to a hospital for diagnostic work-up [1].

In 2019, the detection and recall rates of the programme were 6.9 per 1000 women screened and 2.4%, which are among the highest and lowest, respectively, in Europe [2, 3]. Due to workforce issues, the screening interval has increased over the last years (towards 32 months), thereby increasing the detection rate to 7.9 per 1000 in 2022 at the same recall rate [4].

However, the 2D nature of DM results in well-known limitations [5]. Digital breast tomosynthesis (DBT) is an imaging technique that has been developed as a potential alternative to DM. Multiple studies have concluded that DBT improved screen-detected breast cancer rates, but that no effect has been seen on interval cancer (IC) rates [6, 7]. However, it should be noted that only two studies with DBT plus synthetic mammography (SM) reported IC rates [7]. Houssami et al also emphasised that their results were derived from studies on initial DBT examinations and that results on subsequent examinations may be different.

On average, DBT screening in European trials was found to increase the cancer detection rate to an average of 7.2 per 1000 for biennial screening [7]. Since the Dutch programme already nearly reaches this detection rate with biennial DM, it is unclear if DBT would increase detection. In addition, in Europe, recall rates for DBT screening decreased or increased, depending on the baseline DM recall rate [8]. Therefore, the already-low recall rate in the Netherlands could be expected to increase with DBT screening, but it is unknown to what extent. It is important to investigate the effects and acceptability of DBT in the Dutch screening setting to predict if DBT would be cost-effective [9, 10].

For DBT screening in the Netherlands to be feasible from an economic and human resources point of view, the interpretation of DBT cases must be optimised, to result in an acceptable reading time [11]. Options available for reducing reading time include using the MLO view without the CC view [5], 6 mm slabs instead of 1 mm slices [12], or using AI-aided navigation [13]. In addition, replacing one of the readers with AI could also be an option to further reduce the radiologist’s workload [14]. Potentially, one or a combination of these approaches could reduce the DBT reading demands to even below those currently required in DM screening.

Therefore, the aim of the Screening Tomosynthesis trial with advanced REAding Methods (STREAM) is to determine the short-, medium-, and long-term outcomes and cost-effectiveness of nationwide DBT breast cancer screening in the Netherlands, when an optimal image acquisition and interpretation strategy is used, and to ensure its acceptability by the various stakeholders. Short-term indicators for the study are participation rate, prevalent recall rate, detection rate, and positive predictive value of DBT screening. Medium-term indicators comprise the advanced cancers (ACs) (stage ≥ II) detected in the second round of DBT screening, IC rate, and incident recall rate. Long-term indicators are predicted breast cancer mortality, number of cancers overdiagnosed, and cost-effectiveness.

## Methods and analysis

The Minister of Health, Welfare and Sport has granted ethical approval and a license to conduct this trial from 1 May 2023 to 1 June 2028 (Registration number: 3574709-1044141-PG). This is considered equivalent to approval by an institutional review board.

### Study design

STREAM is a prospective, non-randomised, parallel-group population-based trial embedded in the Dutch programme. The intervention arm will consist of 17,275 participants undergoing two rounds of DBT imaging and the control group will consist of 86,400 participants undergoing two rounds of DM screening acquired around the same time as the DBT examinations (Fig. 1).

**Fig. 1 Fig1:**
[figure not shown]
Flowchart of the recruitment and data collection in the two screening rounds of the STREAM trial

### Data collection

#### Population and recruitment strategy

In collaboration with the Dutch Cancer Screening Organisation (BVO-NL, due to its name in Dutch), three mobile and three fixed screening units throughout the Netherlands were selected to perform DBT screening based on geographical spread, availability, and capacity. All women between the ages of 49 and 72 who are due for screening in one of these units will receive an invitation to participate in the intervention arm of the STREAM trial. Invitations are sent with the invitation for screening and include an information leaflet and informed consent form. Women who decide to participate in the trial must provide written informed consent. Inclusion of participants started in July 2023 and was completed in May 2024. The only exclusion criterion is being wheelchair-bound, because of practical reasons. Participants will be re-invited for a second round of DBT screening, approximately two years later. See Fig. 1.

The control arm will be selected to be representative of the population of the intervention arm, with respect to age, region, and screening interval, but screened at different units. For the control arm, aggregated data will be received on the same parameters as the intervention group including follow-up. In the Netherlands, informed consent is implied for the use of pseudonymised or aggregated cancer screening data when one takes up the offer of screening unless the individual specifically opts out. Individuals who withdrew consent will not be included in the control arm.

#### Training

All radiographers and screening radiologists involved in the STREAM trial were trained before the start of recruitment. A one-day training was organised at the Dutch Expert Centre for Screening (LRCB) for the screening radiologists. The radiographers attended an online information meeting organised by BVO-NL and LRCB and were subsequently trained by BVO-NL and the application specialist of the system vendor.

#### Image acquisition

At the screening unit, the participants undergo two-view DBT imaging (i.e., CC and MLO views) of both breasts using the imaging systems currently in use by the programme (Selenia 3Dimensions, Hologic Inc.).

#### Image interpretation

In addition to the reconstruction of the DBT images from the acquired projections, the acquisition systems generate the corresponding SM images for the four views, all of which are made available to the interpreting radiologist. If available, DM images of previous screening examinations are used for comparison. DBT images are independently double-read, just like DM images are in the regular programme [15]. Discrepancies between the two radiologists are solved by arbitration or consensus, also as per current practice.

#### Acceptability for participants

After the DBT examination, participants are asked to complete either a web- or paper-based (according to their preference) questionnaire about the acceptability of DBT screening. Questions include topics on the experience of undergoing DBT screening, comparison to previous experience with DM, if any, intention to participate in subsequent DBT screening, suggestions for improvement, perceived pain or discomfort, and anxiety experienced during the DBT examination [16] (see Supplementary Appendix A). After the second round of DBT screening, participants will be asked to complete another comparable questionnaire.

In addition, radiographers and radiologists involved in the trial are asked to complete a questionnaire after the first and second rounds of DBT examinations. These questionnaires include questions about workflow, acquisition, perceived reading time, preferences, and suggestions for improvement (see Supplementary Appendix B).

A plan of action will be made to overcome the identified barriers based on the answers given in the questionnaires after the first round of DBT screening by participants, radiographers, and radiologists. When possible, improvements will be made for the second round of DBT screening. Questions about the effectiveness of the improvements will be added to the questionnaires after the second round of DBT screening.

#### Sample size calculations

Sample size calculations were done in G*Power (version 3.1.9.4. using an alpha of 0.05, a beta of 0.20, two-sided *Z*-test and an allocation ratio for the control/intervention group of 5) based on the primary outcome measure; i.e., the sum of the IC and advanced cancer (AC) rate at the seco nd round (combined endpoint) in the DBT group compared to the control group. We powered the trial to detect a reduction in the primary outcome measure of 1.3 per 1000, which reflects a difference of 36% from this combined endpoint with DM (3.6 per 1000) (see further details in Supplementary Appendix C). This requires a sample size for the intervention group in the second round of 17,275 screening examinations with DBT. Assuming 95% re-attendance, this requires 18,184 screening examinations with DBT in the first round. The sample size for the control group is five times that of the intervention group in the second round, i.e., 86,375 participants screened with DM. Again, assuming a 95% re-attendance rate, 90,693 participants are required. For practical reasons, the sample sizes for the first round were rounded off to 18,200 in the intervention group and 91,000 in the control group.

## Data analysis

### Statistical analyses

The IC rate will be defined as the number of cancers, both in situ and invasive, diagnosed clinically (i.e., outside of screening) after a negative DBT in the first, second, and third year after the first screening round of the trial per 1000 screens (considering the longer screening interval). The AC rate will be defined as the number of tumours stage II or higher (TNM classification [17]) diagnosed after recall in the second screening round of the trial per 1000 screens. Data on screen-detected cancers (SDC) and IC, as well as their characteristics (e.g., stage and grade), will be obtained through linkage with the Netherlands Cancer Registry and the Dutch nationwide pathology databank for the intervention as well as the control group.

Secondary outcome measures including participation rate (i.e., percentage of participants in DBT or DM screening of the population invited), recall rate (i.e., number of women recalled for further examination per 1000 women screened), detection rate (i.e., number of women with SDC per 1000 women screened), and positive predictive value (i.e., percentage of women with SDC of women recalled) will be calculated for both screening rounds separately. The recall rate in the first round is expected to be higher due to the first-round effect of a more sensitive screening test, the learning effect for the radiologists, and the absence of prior DBT screens to compare to [18, 19]. The recall rate of the second round will estimate the long-term recall rate for DBT screening. The detection rate will be calculated for invasive and in situ cancers, overall and for cancer stage II or higher. Screening outcomes of both rounds will be stratified by breast density, as assessed by automated methods by Volpara (Mātakina Technology) and Quantra (Hologic).

Screening outcomes for the two groups will be compared using the *χ*^2^ test to test differences between proportions and rates, overall and stratified by screening interval and breast density. The Fisher exact test will be used in stratified analysis with small groups. 95% confidence intervals will be calculated to consider the variability of proportions and rates. In addition, logistic regression analysis will be used to compare the results in the intervention and the control group by calculating the relative rates of the main screening detection measures, with 95% confidence intervals. The pain (scale 0–10), discomfort, and anxiety scores (4-point Likert scale) experienced in DBT screening will be compared to the experience of previous DM screening with paired *t*-tests and to scores on DM screening reported by a reference population with independent *t*-tests. A *p*-value ≤ 0.05 will be considered to indicate a statistically significant difference. Qualitative analyses in ATLAS.ti will investigate the answers to open questions on acceptability among participants, radiologists, and radiographers using inductive reasoning.

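### In round 1 the DBT participation rate combines screening attendance with written trial consent, so it is not comparable with the DM rate and does not measure participation in DBT screening

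*Protocol article*

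**What the plan says.** The Statistical analyses section of the protocol article lists, among the secondary outcomes to be calculated for each round, "participation rate (i.e., percentage of participants in DBT or DM screening of the population invited". The Introduction states what it is for: "Short-term indicators for the study are participation rate, prevalent recall rate, detection rate, and positive predictive value of DBT screening".

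The section Population and recruitment strategy describes how women enter each group.

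- **DBT.** Eligible women "who are due for screening in one of these units will receive an invitation to participate in the intervention arm of the STREAM trial". The mailing is combined with the routine one: "Invitations are sent with the invitation for screening and include an information leaflet and informed consent form". Then: "Women who decide to participate in the trial must provide written informed consent".
- **DM.** There is no trial consent step. For these women, "informed consent is implied for the use of pseudonymised or aggregated cancer screening data when one takes up the offer of screening", unless they opt out.

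The Abstract describes the controls as "86,400 women selected from the database of the Dutch breast cancer screening programme screened with digital mammography". The recruitment section adds that they come from other units and that aggregate data covering the same items as in the intervention arm will be obtained for them.

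**The concern.** The two rates share a name and a nominal denominator, but their round-1 numerators count different things. The DM numerator needs one act, attending. The DBT numerator needs two, attending and signing a research consent form. A woman invited at a STREAM unit who would attend screening but does not want to join a study counts as a non-participant in the DBT rate, although she has not refused screening and may not have refused tomosynthesis.

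A nationwide DBT programme would have no trial-consent step, so the round-1 figure does not estimate the quantity the Introduction names. The risk is in interpretation: a lower DBT figure could be read as women being less willing to be screened with DBT, in a trial meant to inform a decision on implementation.

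**Working it through.** **Is there a figure to reproduce?** No. The article gives no expected participation rate, no usual attendance and no consent uptake. The only attendance figure is the 95% re-attendance in Sample size calculations, which concerns round 2 and is applied to both groups (for DBT, 17,275 / 0.95 = 18,184, as stated).

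**Inputs.**

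- a = proportion of invited women who would attend usual screening. Assumed 0.65 to 0.80.
- c = proportion of would-be attenders at STREAM units who also give written trial consent. Assumed 0.60 to 0.95.
- True effect of DBT on attendance: set to zero, to isolate the artefact.

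**Formula.** Observed DBT rate = a × c. Observed DM rate = a. Spurious deficit = a − a × c = a × (1 − c).

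**Results, in percentage points of deficit.**

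| a | c = 0.95 | c = 0.90 | c = 0.80 | c = 0.60 |
|---|---|---|---|---|
| 0.65 | 3.25 | 6.5 | 13 | 26 |
| 0.70 | 3.5 | 7.0 | 14 | 28 |
| 0.75 | 3.75 | 7.5 | 15 | 30 |
| 0.80 | 4.0 | 8.0 | 16 | 32 |

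Example: a = 0.70 and c = 0.90 give 0.70 × 0.90 = 0.63, which is 7 points below 0.70.

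**How small a consent loss could be detected, if the rates were tested.** Take the planned round-1 sizes, 18,200 DBT and 91,000 DM, as attenders. The invited numbers are then 18,200 / a and 91,000 / a. At a = 0.70 these are 26,000 and 130,000. The standard error of the difference is √[0.70 × 0.30 × (1/26,000 + 1/130,000)] = 0.0031. The difference detectable with 80% power at two-sided 0.05 is (1.96 + 0.8416) × 0.0031 = 0.0087, or about 0.87 points. Over a = 0.65 to 0.80 it is about 0.8 to 0.9 points. Divided by a, that is a consent loss of only about 1 to 1.4% of would-be attenders.

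**Round 2.** Only round-1 participants are re-invited to DBT. The DBT rate is then re-attendance among women who have already attended and consented. Its natural comparator is re-attendance of round-1 DM attenders. Sample size calculations assumes 95% re-attendance in both groups, so the plan appears to think of round 2 in this way, but the single definition of participation for both rounds does not say so.

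**The case against.** Several stronger readings are tempting, and the documents do not support them.

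- **Controls are attenders only, so they have no invited denominator.** A reader might infer this from the Abstract ("The control group will consist of 86,400 women selected from the database of the Dutch breast cancer screening programme screened with digital mammography"). But the definition puts both modalities over the invited population, and the aggregate control data could include numbers invited. The control denominator is unspecified; it is not shown to be attenders only.
- **A large gap the other way in round 2.** Setting 95% re-attendance in the DBT group against an assumed 70% programme attendance would give 25 points. The article never pairs those quantities.
- **Harm through the long-term model.** Microsimulation modelling lists recall, detection and interval cancer rates as the performance data used to update the model. Participation is not among them.
- **A highly significant chi-squared result.** The comparison paragraph speaks generally of screening outcomes, stratified among other things by breast density, which is not measured in non-attenders. A test of participation is a possible broad reading, not an explicit plan.

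There are two further defences. First, the definition could be read as attendance by either modality among invited women, which would already be the remedy; the Introduction's description of participation as an indicator of DBT screening points the other way. Second, a journal article may leave exact numerators and denominators to a fuller document. That excuses missing detail. It does not remove a mismatch that follows from the definition and the consent process as both are stated here.

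It also stands that the size rests wholly on assumed values, and that the written-consent step is visible to an attentive reader.

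**Conclusion.** The point holds for round 1. As written, the DBT participation rate is attendance multiplied by consent uptake, and the DM rate is attendance alone. The two are not comparable, and the first does not measure participation in DBT screening. The direction is certain whenever consent uptake is below 100% and DBT has no effect on attendance.

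The size cannot be fixed from the documents. With assumed usual attendance of 0.65 to 0.80, it is about 3 to 4 points at 95% consent uptake and 6.5 to 8 points at 90%. For round 2 the need is only to state which rate is meant. The primary endpoint and the recall, detection and predictive-value outcomes do not use this definition.

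**What to change.** 1. Define round-1 participation as attendance at any screening, DBT or DM, among all women invited at the six STREAM units. Compare it with attendance among all women invited at the control units in the same period.
2. Report trial-consent uptake at the STREAM units separately, labelled as a recruitment figure and not as participation in DBT screening.
3. For round 2, state that the rate is re-attendance of round-1 attenders in both groups, consistent with Sample size calculations.

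The cost is a change of wording plus aggregate counts of women invited and attending at both sets of units. No new data from participants are needed. A small limitation remains: attendance at the STREAM units may itself be influenced by receiving a trial invitation, so even the revised comparison is not a pure effect of DBT, and this should be said when it is reported.

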## Discussion

The major strength of STREAM is its prospective parallel-group design and its real-world evaluation of different reading strategies. To the best of our knowledge, no prospective trial has evaluated different reading methods for DBT on such a large cohort. This design will give insights into the implementation and acceptability of DBT in the population screening practice.

There are a few limitations to this trial. First, the reader study sessions will start after the first round of data is collected. At that moment, we will not yet have information on ICs. Therefore, the AI solutions will be evaluated on recall and breast cancer detection data from round 1 only. We will re-evaluate the AI solutions once round 2 is completed, but we cannot redo the reading strategy analysis in the funding period. The second evaluation will, therefore, only serve to check if there are significant differences in the results of the AI predictions. This could mean that if a reading strategy including AI is selected as optimal, that strategy does not consider the fact that the AI could be detecting ICs that have not been detected yet. This in turn might influence the evaluation of normal reading versus optimal reading strategy.

Furthermore, in the first round of this trial, there are no previous DBT images available to compare against the current case. Instead, the radiologists are provided with the previous mammogram. Therefore, the first round does not really reflect the possible future steady state in which all priors would consist of DBT images. The second round will have previous DBT images available and will reflect the future steady state more accurately.

The results from the STREAM trial will indicate whether it is beneficial to implement DBT screening in the Netherlands by looking at short-, medium-, and long-term effects, optimal reading strategies, cost-effectiveness, and the acceptability of various stakeholders. In addition, these results will be relevant for other countries considering implementing DBT in screening.

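### Separate DBT-versus-DM significance tests within density and interval strata cannot show whether the DBT effect differs between strata; one interaction test per stratifier would

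*Protocol article*

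**What the plan says.** All of this is in the Protocol article.

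- **Stratified tests (Statistical analyses).** Screening outcomes in the two groups are compared with the χ² test to "test differences between proportions and rates, overall and stratified by screening interval and breast density". Fisher's exact test replaces it in stratified analyses with small groups. That indicates a separate test inside each stratum, not one pooled stratified test.
- **Decision rule (same section).** One sentence covers every test: a p-"value ≤ 0.05 will be considered to indicate a statistically significant difference".
- **Density (same section).** "Screening outcomes of both rounds will be stratified by breast density, as assessed by automated methods by Volpara" and also by Quantra. Neither tool is named as the main one.
- **Model (same section).** Logistic regression is planned to compare the intervention and control groups as relative rates. Its stated purpose is the group comparison, not a comparison of effects between strata.
- **Power (Sample size calculations).** The trial is sized "using an alpha of 0.05, a beta of 0.20, two-sided" Z-test, with "an allocation ratio for the control/intervention group of 5", "to detect a reduction in the primary outcome measure of 1.3 per 1000", described as "a difference of 36% from this combined endpoint with DM (3.6 per 1000"). This covers the overall primary comparison only.

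**The concern.** A reader of stratified screening results will want to know whether the DBT effect differs by breast density or by screening interval. Testing DBT against DM separately in each stratum answers another question: whether that stratum, taken alone, has enough evidence against no difference. A significant result in one stratum and a non-significant result in another is not evidence that the effects differ. When the whole cohort has only 80% power, such a split is to be expected even if the effect is the same everywhere.

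The stratifiers, the test and the threshold are all stated, so an analysis that followed the text would produce this pattern of verdicts. Two density tools of equal standing add a choice between two sets of density results. What is at stake is the reading of the stratified tables: a split caused by low power could be taken as a sign that DBT works in only some groups of women.

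**Working it through.** **Inputs.** From Sample size calculations: DM rate 3.6 per 1000; reduction 1.3 per 1000, so DBT rate 2.3 per 1000; two-sided alpha 0.05; power 0.80; five controls per intervention participant; 17,275 and 86,375 women in the second round. The article does not give the number or shares of strata, so two to four strata are assumed, with the 5:1 ratio kept in each.

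**Step 1: reproduce the plan's figure.** Pooled two-proportion Z-test:

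- pooled rate = (0.0023 + 5 × 0.0036)/6 = 0.003383
- s0 = √(0.003383 × 0.996617 × 1.2) = 0.06361
- s1 = √(0.0023 × 0.9977 + 0.0036 × 0.9964/5) = 0.05488
- n = (1.960 × s0 + 0.8416 × s1)² / 0.0013² = 17,275

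This equals the stated number, so the overall comparison uses all of the planned power. The expected DBT event count is 17,275 × 0.0023 ≈ 40 in total.

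**Step 2: power within a stratum holding share s, same effect.**

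power(s) = Φ[(0.0013 × √(17,275 s) − 1.960 × s0) / s1]

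For s = 0.5: √8,637.5 = 92.94, so the argument is (0.1208 − 0.1247)/0.05488 = −0.07, and power is 47%. The other shares give 56% (s = 0.6), 38% (0.4), 32% (one third), 24% (0.25) and 10% (0.1).

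**Step 3: chance of conflicting verdicts.** Strata are independent, so P(some but not all significant) = 1 − P(all significant) − P(none significant), each a product of the powers or their complements.

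| Assumed strata | Power per stratum | All significant | None significant | Conflicting |
|---|---|---|---|---|
| 50/50 | 47%, 47% | 22% | 28% | 50% |
| 60/40 | 56%, 38% | 21% | 28% | 51% |
| 3 equal | 32% each | 3% | 32% | 65% |
| 4 equal | 24% each | 0.3% | 34% | 66% |
| 10/40/40/10 | 10%, 38%, 38%, 10% | 0.1% | 31% | 69% |

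Simulating 200,000 trials per row with binomial counts gives nearly the same values: stratum power 39% to 56% in the two-stratum rows, and conflict in 50%, 51%, 66%, 66% and 69%. Doubling the baseline risk in the 40% stratum while keeping the rate ratio at 0.64 also leaves conflict at about 51%.

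**Step 4: the alternative.** In the same simulated trials, a single heterogeneity test across strata was falsely positive in 3.0% to 4.4%. A separate simulation with four density strata gave 3% to 5% across the primary endpoint and a recall-type outcome (24 per 1000).

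**Step 5: no DBT effect at all.** At least one stratum is significant in either direction in about 10% (two strata), 14% to 15% (three) or 18% (four) of trials. A stratum falsely favouring DBT appears in only about 4%, 6% and 7%.

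**The case against.** **The article is a condensed protocol.** The full protocol or analysis plan may add an interaction term or label the strata exploratory. This stands for matters on which the article is silent, and is why no request is made here for a multiplicity scheme or a testing hierarchy across the secondary outcomes. It does not remove the point: the article itself fixes stratum-wise tests and a threshold for calling them significant, and a better method for the same purpose is available at almost no cost.

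**No subgroup decision is announced.** This also stands. The Discussion says that the results "will indicate whether it is beneficial to implement DBT screening in the Netherlands by looking at short-, medium-, and long-term effects", and continues with reading strategies, cost-effectiveness and acceptability; subgroups are not listed. The Microsimulation modelling section names no stratum-specific inputs. Screening interval is also a factor on which controls are selected, so stratifying by it may partly serve comparability. A reader might infer that the trial intends to target or withhold DBT by density, but the article does not say so.

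**A tempting stronger reading is that false positives drive the problem.** They do not. With no effect, a stratum wrongly favours DBT in only about 4% to 7% of trials. The 50% to 69% conflict rates arise when DBT works equally everywhere and each stratum is underpowered. Tightening alpha would lower stratum power further, so alpha control is not the remedy.

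**Two density tools need not mean two sets of tests.** The article names both tools for stratifying outcomes but does not say that both define strata for the between-group tests. It is enough that neither is ranked.

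**Conclusion.** The point holds as an improvement to the analysis of strata. As stated, the stratum-wise tests cannot show whether the DBT effect differs by density or interval. With a uniform effect of the design size they would give conflicting verdicts in about half of trials with two strata and about two thirds with three or four, against about 3% to 5% false signals from a heterogeneity test.

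This rests on assumed numbers and shares of strata, and on the combined interval and advanced cancer endpoint, the only outcome for which the article gives design figures. Outcomes with more events, such as recall, would have different conflict rates, but the reasoning is the same. The problem is present from two strata upward.

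A reader might also infer that the trial's main conclusion is at risk. It is not: the overall primary comparison is one test at 0.05, and its type I error and power are unchanged.

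**What to change.** In the Statistical analyses section, or in the analysis plan that implements it:

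1. Replace the significance tests within strata by one arm-by-stratum interaction test per stratifier (screening interval, breast density) in the logistic regression already planned.
2. Report stratum-specific estimates with 95% confidence intervals, labelled exploratory, without a significance verdict for each stratum.
3. Name either Volpara or Quantra in advance as the main density stratifier, and use the other as a sensitivity analysis.

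The cost is wording and one model term per stratifier. The control data can stay aggregated, because the counts by arm and stratum already needed for the stratified χ² tests are enough to fit the interaction. The downside is that interaction tests have low power, so fewer subgroup results can be called significant, and a non-significant interaction must not be read as proof of equal effects.
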